**Additional data**					
Demographic data	Socio-demographic characteristics in epidemiological studies (SDD)	X		X	X

#### Points of measurement

Prior to the intervention, baseline data will be collected. During the following intervention period, for each patient of the intervention and control group, primary outcomes will be measured at four points in time: at admission to (T0) and discharge from hospital (T1) as well as 6 and 12 months after discharge from the hospital (T2 and T3).

### Blinding

Patients, pharmacists, physicians, study assistants, and statisticians will not be blinded. Only at T2 and T3, pharmacists will be blinded for data collection.

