### Intervention

During in-patient treatment of patients affected by polypharmacy, a pharmacist specially trained in communication skills performs a *narrative-based medication review*. Thus, two approaches are combined here: the face-to-face clinical “brown bag” medication review [42] and the patient-centered approach of narrative medicine [43,44]. Apart from detecting potentially inadequate medication, a major aim is to identify patient preferences and to include them—whenever possible—into a hierarchically structured list of evidence-based medication recommendations. Thus, priorities for medication modification can be based on both “objective” pharmaceutical considerations as well as on “subjective” patient preferences. The pilot study showed that this approach motivated patients to actively contribute to the reduction of medication. The *narrative-based medication review* itself takes approximately 30–45 min. The pharmacist then prepares a list of possible drugs to be stopped. Pharmacists have access to a clinical decision support system [45]. The list will be discussed with the hospital physician in charge and will be submitted for adjustment with the patient’s individual GP. The active involvement of the patient’s GP aims at bringing transparency into the decision-making and might increase chances for a sustainable optimization of medication by preventing relapse to old medication patterns (as frequently observed in other studies). See Figure 1.

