#### Secondary outcomes

The secondary outcomes are appropriateness of prescribed medication (PRISCUS list [22], Beers Criteria [49,50], MAI [51,52]), patient satisfaction (TSQM) [53,54], patient empowerment (PEF-FB-9) [55], patient autonomy (IADL) [56], falls (frequency and severity) [57], re-hospitalization, and death. For all patients ensured with the largest public German health insurance provider AOK, cost-effectiveness will be analyzed by the Scientific Institute of the AOK (WIdO). In addition, data on socio-demographic characteristics [58] will be collected. See Table 1.

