**Secondary outcomes**					
Appropriateness of prescribed medication	PRISCUS list, Beers Criteria	X	X	X	X
	Medication appropriateness index (MAI)	X	X	X	X
Patient satisfaction	TSQM	X		X	X
Patient empowerment	9-item shared decision-making questionnaire (PEF-FB-9)	X		X	X
Patient autonomy	Instrumental activities of daily living scale (IADL)	X		X	X
Falls	*Frequency*: number of falls in the previous 6 months	X	X	X	X
	For each fall, *severity* will be assessed:				
	*Moderate*: bruising, sprains, cuts, abrasions, or reduction in physical function for at least three days or if participant sought medical help				
	*Severe*: fractures, admission to hospital with an injury, or if stitches were required				
Re-hospitalization				X	X
Death			X	X	X
Cost-effectiveness	Difference in health care costs between both groups				X

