**The flowchart.**

### Data collection, quality, and monitoring

The personnel of the participating wards will not be involved in data collection. Instead, data collection will be performed by trained pharmacists and study assistants. Pharmacists will also perform telephone data collection at T2 and T3 and will not receive information about group affiliation of patients. To reduce selection bias, a standardized and scrupulously followed recruitment procedure will be employed, supervised by research assistants and monitored by the Clinical Trial Center North at the University Hospital Hamburg-Eppendorf (CTCN). Monitoring will be conducted according to the standard operation procedures of the Clinical Trial Center North and in compliance with the E6 ICH GCP guideline for good clinical practice. Clinical monitoring will also include review and resolution of missing or inconsistent results and source document checks (i.e., comparison of submitted study results to original reports) to assure the accuracy of the reported data.

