### Statistical methods

The unit of inference will be the individual. Then, analyses will be carried out at cluster and at individual level. In a first simple approach, data in each cluster will be collapsed to construct a relevant summary measure (mean with standard deviation). This essentially removes the need to adjust for clustering effects. Of course, for variable-sized clusters, this analysis does neither take into account the intra-cluster correlation nor the cluster sizes and is less efficient than an individual-level analysis. But nevertheless, the relative simplicity of a cluster-level analysis still remains an advantage, albeit with some loss of efficiency and an inability to adjust for individual-level risk factors. In a second step, generalized estimating equations (GEE) models will be applied [60,61]. A generalized linear model takes into account within-group correlation and allows adjustment for the joint effects of cluster-level as well as individual-level factors without the requirement of parametric assumptions.

A model that takes into account the randomized clusters (wards) as random effect, with EQ-5D change or difference in prescribed long-term pharmaceutical agents between intervention and control at T3 as dependent and random group as independent variables, will be fitted to the data. In this model, baseline (T0) values of primary variables and a selection of further baseline characteristics of ward or patient will function as covariates. The intervention effects are quantified by the between-group differences of the corresponding estimates of changes from baseline from the fully adjusted model, which we assume to give the best account of the study results. In the statistical analyses, missing values will not be replaced. Methods for dealing with outliers will be defined in the statistical analysis plan (SAP) or in an addendum to the SAP. Secondary efficacy variables will be analyzed in an explorative way. Similarly, confidence intervals computed will be interpreted as interval estimates for presence or absence of effects in the study data. Intention-to-treat analyses will be performed.

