## Discussion

The POLITE-RCT trial focuses on the pressing challenge of reducing inappropriate medication among elderly patients suffering from chronic diseases. The setting of the study, the German region of Mecklenburg-Western Pomerania offers the particular chance to study the effectiveness of the proposed intervention in an area particularly affected by population aging and an increasing number of people with chronic diseases and multimorbidity [62].

The intervention concept of POLITE-RCT is innovative; as hospitalization of older, multimorbid, and chronically ill patients is often related to an increase in the number of prescribed long-term drugs [39,40], the focus on the interface between secondary and primary health care is particularly promising. To our knowledge, this is the first trial that systematically assesses the effectiveness of a *narrative-based medication review* performed by trained pharmacists. Pharmaceutical recommendation will be based on both *evidence and patient preferences*.

Major methodological strengths of the trial include external monitoring as well as stratified randomization of participating wards after baseline data collection. This way, imbalances between intervention and control group will be minimized. Also, based on baseline data, sample size requirements will be adapted.

Potential sources of bias include, e.g., the risk of contamination between intervention and control wards, interviewer bias, and the risk of low inter-rater reliability. To reduce the latter, pharmacists will regularly discuss patient cases and will decide about controversial cases by consensus.

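### The plan does not prevent medication appropriateness at discharge (T1), chiefly the MAI, from being scored with the arm known

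*Protocol article*

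**What the plan says.** The Blinding section of the protocol article sets the general position: "Patients, pharmacists, physicians, study assistants, and statisticians will not be blinded". The only exception follows: "Only at T2 and T3, pharmacists will be blinded for data collection". The section on data collection, quality and monitoring keeps ward staff out of data collection and states instead that "data collection will be performed by trained pharmacists and study assistants". It adds that the T2 and T3 telephone collection is done by pharmacists who are not told the patient's group.

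Table 1 marks PRISCUS, Beers and MAI at all four time points: T0 (admission), T1 (discharge), T2 and T3. In the Intervention section a pharmacist conducts the medication review, after which "The pharmacist then prepares a list of possible drugs to be stopped". The Discussion lists interviewer bias and low inter-rater reliability among the possible sources of bias. It offers a remedy for the second only: "pharmacists will regularly discuss patient cases and will decide about controversial cases by consensus". On the analysis, the Statistical methods section says: "Secondary efficacy variables will be analyzed in an explorative way".

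**The concern.** The intervention is itself a judgement about which drugs a patient could do without. Appropriateness at discharge is a judgement about the regimen that results. If both come from people who know the arm, and possibly from the same person, the T1 score can favour the intervention arm without any real difference in prescribing. In the control arm no study pharmacist has shaped the regimen, so the rater has no comparable stake in it. A bias of this kind differs by arm, and neither randomisation nor a larger sample removes it.

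T1 is the measurement closest to the intervention and so the earliest view of whether prescribing improved. The plan accepts the case for masking at T2 and T3 but does not extend it to T1. Yet a regimen, unlike a patient interview, can be rated later from a written list.

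**Working it through.** No figure in the article depends on who is blinded for these ratings, so the check is mainly a comparison of sections.

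1. **Who can collect T1 data?** Pharmacists or study assistants; ward staff are excluded (Data collection section).
2. **Are they masked at T1?** Both groups are named as not blinded, and the exception covers pharmacists at T2 and T3 only (Blinding section). T1 collection is therefore open whichever group does it.
3. **Is appropriateness measured at T1?** Yes, by all three instruments (Table 1).
4. **Could the rater have shaped the regimen?** A pharmacist writes the stop list (Intervention section), and pharmacists also collect data. No section separates the two tasks for a given patient, and none says that they coincide.
5. **Which instruments leave room for judgement?** The Background describes Beers as a catalogue of criteria and PRISCUS as a published list agreed by experts. Checking drugs against either leaves less discretion, so the point rests mainly on the MAI.
6. **Does the consensus procedure help?** Discussion can bring raters closer together. It cannot remove an expectation they share because they know the arm.
7. **Does the same argument apply at T0?** Not the part about rating one's own recommendations, because T0 is at admission, before the review. In the six-month baseline period no arm exists yet. In the intervention period the ward's allocation is already fixed at T0, so the arm can be known.
8. **Could the ratings be masked?** Control-arm medication data come from patient records (Control group section), so rating from records is feasible in principle.

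*Illustration of scale only.* The article gives no MAI standard deviation or intra-class correlation, so the figures below borrow those of the primary outcomes and assume the bias.

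- Plan's own figure: the standardised difference is 0.1/0.3 = 0.5/1.5 = 0.33. The normal formula 2 × (1.96 + 0.84)² / 0.33² gives 142 per group, and the t-test gives 142.2, hence the stated 143. Then 2 × 143 × 5.4 = 1,544.4, hence the stated 1,545.
- Effective size per group: 1,545 / 2 / 5.4 = 143. Standard error of a difference in SD units: √(2/143) = 0.118.
- With no true effect and a rater bias of b SD, the chance of two-sided p < 0.05 is 1 − Φ(1.96 − b/0.118) + Φ(−1.96 − b/0.118). For b = 0.1, 0.2 and 0.3 this is about 14%, 39% and 72%, against a nominal 5%.
- The stated ICC of 0.1 and cluster size of 40 would give a design factor of 1 + 39 × 0.1 = 4.9 rather than 5.4. With 4.9 the three figures are about 14%, 43% and 76%. That discrepancy is a separate matter and does not bear on this point.

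**The case against.** The strongest reply is that a condensed article need not name the rater, and that Table 1 gives the time point a medication list refers to, not the moment it is scored. Scoring may take place later and under masking, as a full protocol might specify. In part this stands: the article does not say who scores, when, or from what material. It does, however, state outright that both groups of collectors are open and confines the exception to T2 and T3. Open status at T1 is thus a stated choice and not just omitted detail.

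Several stronger readings are tempting and are not supported:

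- A reader might infer that pharmacists score the results of their own recommendations. No section says so; the plan merely fails to rule it out.
- A reader might take the consensus discussions to be held by arm-aware pharmacists about MAI scores at T1. The Discussion mentions neither the instrument nor the time point.
- A reader might treat the T0-to-T1 change in appropriateness as the decisive test of the intervention. The article does not define it as an endpoint. Appropriateness is secondary and exploratory, the primary comparisons are at T3, and the aim is a sustained reduction.
- A reader might express an assumed rater shift as a share of the 0.33 SD used for sizing. That effect belongs to EQ-5D and the number of agents, not to the MAI, so the ratio would say nothing about this outcome.

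**Conclusion.** The point holds in limited form. The plan explicitly leaves T1 data collectors aware of the arm and does not keep the reviewing pharmacist from rating the discharge regimen, so a T1 difference in MAI could partly reflect the rater. PRISCUS and Beers are less exposed. The appropriateness scores form no part of either primary outcome, so the T3 primary comparisons are not put in doubt by this route, and no sample size, power or alpha changes.

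The size of the bias is unknown. The illustrative error rates show only that, at this sample size, a modest arm-related shift could pass for an effect; they are not an estimate for this trial. The conclusion assumes that MAI scoring involves rater judgement, which fits the Discussion's worry about inter-rater reliability, and that no masked T1 rating is laid down in a document not shown.

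**What to change.** Amend the Blinding section as follows.

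- At T0 and T1, collect the medication and diagnosis lists.
- Have at least the MAI rated from those lists with arm, ward and time point removed, in random order, by an existing study pharmacist who did not review that patient. Including T0 means that both time points are scored in the same way.
- Hold any consensus discussion on the masked lists.

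The cost is some data handling to mask and shuffle the lists, and scores that arrive later. The article gives no staffing figures, so availability of a second pharmacist is an assumption. It is a reasonable one, since the Discussion has several pharmacists conferring and two centres take part. Masking may be imperfect if the content of a list hints at the arm, but it removes the explicit label and separates author from rater.

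If this is not done, name the rater, report the T1 MAI comparison as open-rated, and interpret it as such.

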### Sample size

For the two independent primary outcomes of (1) health-related quality of life (EQ-5D) and (2) the difference in prescribed long-term pharmaceutical agents between intervention and control group at 12 months after discharge (T3), the following assumptions are made: for the single summary index of the five dimensions of the EQ-5D descriptive part (using reference value sets for Germany) for the changes from T0 to T3, a mean clinical relevant difference of 0.1 with standard deviation of 0.3 shall be demonstrated between intervention and control. For the difference in prescribed long-term pharmaceutical agents between both groups at 12 months after discharge (T3), a mean difference of 0.5 (number of agents) in reduction of agents with an expected standard deviation of about 1.5 has to be proven. If an EQ-5D difference of 0.1 with standard deviation of 0.3 (or a mean difference of 0.5 in reductions of agents with an expected threefold standard deviation) is to be demonstrated with a power of 80% at a significance level of 5% two-sided, a sample size of 143 per group will be required in a randomized trial. For the cluster randomized trial, this sample size has to be multiplied by a design factor of 5.4 [59] if an intra-class correlation coefficient (ICC) of 0.1 and a cluster size of 40 patients is assumed, resulting in a sample size of 1,545 evaluable patients in 38 clusters. Assuming a dropout rate of 5%, a total sample size of 1,626 patients in 42 wards has to be recruited initially. The number of patients per cluster was conservatively defined in order to cope with possible variations that could not be taken into account at the start of the trial. Therefore, sample size estimations will be verified by results of the baseline data analysis. If necessary, adjustments of sample size estimations will be realized. See Figure 2.

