### Outcomes

#### Primary outcomes

The independent two main outcomes are (1) health-related quality of life (EQ-5D) [46-48] and (2) the difference in the number of prescribed long-term pharmaceutical agents between intervention and control group at T3. Since in Germany, combination drugs are frequently used, the primary outcome focuses on pharmaceutical agents rather than on number of drugs.

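### Two primary outcomes are each planned at an unsplit 5% with 80% power, and no rule says whether one or both must succeed

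*Protocol article*

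**What the plan says.** The Primary outcomes section opens with "The independent two main outcomes are (1) health-related quality of life (EQ-5D") and adds the number of prescribed long-term agents at T3 as the second. The Sample size section repeats this: "For the two independent primary outcomes of (1) health-related quality of life (EQ-5D) and (2) the difference in prescribed long-term pharmaceutical agents".

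Each outcome has its own target. For EQ-5D, "a mean clinical relevant difference of 0.1 with standard deviation of 0.3 shall be demonstrated between intervention and control". For agents, "a mean difference of 0.5 (number of agents) in reduction of agents with an expected standard deviation of about 1.5 has to be proven". One sample size then serves both. After the EQ-5D assumption comes a parenthesis, "or a mean difference of 0.5 in reductions of agents with an expected threefold standard deviation", and the effect "is to be demonstrated with a power of 80% at a significance level of 5% two-sided". From this follows that "a sample size of 143 per group will be required in a randomized trial", which is multiplied by a "design factor of 5.4 [59] if an intra-class correlation coefficient (ICC) of 0.1 and a cluster size of 40 patients is assumed". The totals are 1,545 evaluable and 1,626 recruited patients.

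The Statistical methods section fits a model with one or the other outcome as dependent variable. It labels only the secondary efficacy variables as explorative, so both primary outcomes remain confirmatory. It leaves the handling of outliers to the SAP and does not mention multiplicity. The Discussion part of the Abstract and the Conclusion both refer to a positive evaluation without defining it.

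**The concern.** With two confirmatory tests, the trial's error rate and power depend on what counts as success. The article sets the level and the power for each test and gives no success rule, so neither figure is established for the trial as a whole.

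A split result is realistic. The two outcomes carry different messages (fewer agents, better quality of life), and a medication review could well change one without a detectable change in the other. The article does not say what to call such a result. Because the Blinding section leaves the statisticians unblinded, a rule chosen after the data are seen would carry little weight.

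**Working it through.** **Inputs (Sample size section).** EQ-5D difference 0.1, SD 0.3. Agents difference 0.5, SD 1.5. Both give a standardised effect of 1/3. Alpha 0.05 two-sided, power 0.80, ICC 0.1, cluster size 40, design factor 5.4, dropout 5%. The correlation between the two test statistics is not given, so 0, 0.3 and 0.5 are assumed.

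**Step 1: reproduce the plan's figures with one outcome at the full 5%.**
- Normal approximation: n = 2 × (1.960 + 0.842)² / (1/3)² = 141.3, so 142 per group.
- Exact t-test: 142 per group gives power 0.799 and 143 gives 0.802, so 143, as stated.
- 2 × 143 × 5.4 = 1,544.4, so 1,545 evaluable.
- 1,544.4 / 0.95 = 1,625.7, so 1,626 recruited.

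An equal split at 2.5% each would give n = 2 × (2.241 + 0.842)² × 9 = 171.1, so 172 per group. Then 2 × 172 × 5.4 = 1,857.6, so 1,858 evaluable, and 1,857.6 / 0.95 gives 1,956 recruited. No split is built into the plan.

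**Step 2: either outcome suffices.** With both null hypotheses true and independent tests, the family-wise error is 1 − 0.95² = 0.0975. A bivariate normal gives the correlated cases.

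**Step 3: both outcomes required.** The type I error is at most 5% without a split. With 80% power for each, independent tests give 0.80² = 0.64; the bivariate normal gives the rest.

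| Correlation | Family-wise error, either suffices | Power for both |
|---|---|---|
| 0 | 9.75% | 64% |
| 0.3 | 9.5% | 67% |
| 0.5 | 9.1% | 69% |

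If only false positives in the direction of benefit are counted, the first entry is 1 − 0.975² = 4.9%, against a nominal 2.5%. The doubling is the same.

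**Step 4: power per outcome at 2.5%, the first step of Holm, with 1,545 evaluable patients.** The design factor for equal clusters is 1 + (m − 1) × 0.1, with m = 1,545 / number of clusters.

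| Basis | Power at 5% | Power at 2.5% | Loss (points) |
|---|---|---|---|
| Plan's factor 5.4, normal | 80.5% | 71.8% | 8.7 |
| 42 equal wards (m = 36.8, factor 4.58), t with 40 df | 84.8% | 76.5% | 8.3 |
| 38 equal clusters (m = 40.7, factor 4.97), t with 36 df | 81.6% | 72.4% | 9.2 |

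The first row belongs beside the plan's 80%, because that 80% was computed with factor 5.4. Unequal wards, or wards randomized together under one senior physician (Clusters section), would lower the other two rows.

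**The case against.** A reader might infer that the trial simply has a false-positive rate close to 10%. The article does not support that as a flat statement, because it never says that either outcome is enough. The parenthetical alternative in the Sample size section can be read as a remark that both outcomes have the same standardised effect and so need the same n. The wording for each target is mandatory and fits a both-required rule at least as well. The Conclusion ties a positive evaluation to a sustainable reduction of polypharmacy, which a significant EQ-5D result alone would not show. All of this stands, so the 9.1% to 9.75% is conditional on an either-outcome rule.

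The second objection is that a testing rule commonly sits in the SAP, which is not shown. This stands in part. An SAP could set a fixed sequence, and 143 per group at 5% would then be valid for the first outcome. But the article itself fixes two confirmatory outcomes, an unsplit alpha and the resulting sample size, and calling the outcomes independent speaks against a hierarchy. A Bonferroni, Holm or both-required rule in the SAP would not carry the article's 80% over to the trial. The Sample size section would still have to be reconciled with it.

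A reader might also infer that the documents require the number of agents to be tested first. The Objectives section points that way. However, EQ-5D is listed first wherever the two appear, and the Background section stresses the lack of evidence on quality of life. The documents do not compel either order.

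**Conclusion.** The point holds in conditional form. As written, the stated 5% and 80% apply to each outcome taken alone and do not together describe the trial. If either outcome suffices, the family-wise error is about 9.1% to 9.75%. If both are required, the error is controlled and the power is about 64% to 69%. These ranges assume correlations of 0.5 to 0 between the test statistics, exactly 80% power for each outcome, and both effects as large as planned. Only an ordered test would keep both 5% for the trial and 80% for the leading outcome, and the article states no order. What is shown is an undefined success rule alongside operating characteristics that depend on it, not a demonstrated 10% error rate.

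**What to change.** Before outcome data are seen, state one confirmatory rule in the protocol and SAP, define a positive evaluation by it, and restate error and power in the Sample size section to match. There are three workable options:

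- **Fixed sequence at 5% two-sided.** No extra patients, and the first outcome keeps its planned power. Number of agents first would fit the Objectives section, but the order is the sponsor's choice. Cost: the second outcome is only exploratory if the first fails, and its chance of confirmation is the joint 64% to 69%.
- **Holm, if each outcome must stand alone.** No extra patients if lower power is accepted. State that power at the 2.5% step is about 72% on the plan's factor of 5.4 (76.5%, against 84.8% at 5%, with 42 equal wards, ICC 0.1 and t with 40 df), a loss of about 8 to 9 points. Restoring 80% at 2.5% on factor 5.4 would need about 1,956 recruited instead of 1,626.
- **Both required.** No split is needed. State joint power of about 64% to 69% in place of 80%.

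Apart from any decision to enlarge the trial, the change is one of wording.

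### The design factor of 5.4 does not follow from the stated ICC of 0.1 and cluster size of 40, which give 4.9; the error is conservative but carries into both patient totals

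*Protocol article*

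**What the plan says.** All the figures stand in one paragraph, Methods, Sample size, of the protocol article.

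- EQ-5D change: "a mean clinical relevant difference of 0.1 with standard deviation of 0.3 shall be demonstrated between intervention and control".
- Number of agents: "a mean difference of 0.5 (number of agents) in reduction of agents with an expected standard deviation of about 1.5 has to be proven". Both outcomes thus have a standardised difference of 1/3.
- The test is planned "with a power of 80% at a significance level of 5% two-sided", for which "a sample size of 143 per group will be required in a randomized trial".
- Clustering: to inflate this number the text uses a "design factor of 5.4 [59] if an intra-class correlation coefficient (ICC) of 0.1 and a cluster size of 40 patients is assumed". The outcome of that step is given as "resulting in a sample size of 1,545 evaluable patients in 38 clusters".
- Dropout: "Assuming a dropout rate of 5%, a total sample size of 1,626 patients in 42 wards has to be recruited initially". The Abstract repeats these last two figures.

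The paragraph adds that the number of patients per cluster was chosen cautiously, to absorb variation that could not be foreseen, and that the estimate will be checked against baseline data and adjusted if needed. It gives no cluster size other than 40, no measure of variation in cluster size, and no formula for the factor beyond the citation. The Clusters section says that wards under the same senior physician are randomized as one unit.

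**The concern.** The text makes the factor conditional on two named inputs, the ICC and the cluster size, and those inputs give a different value. Every number after the factor inherits the discrepancy, including the recruitment target in the Abstract. The stated 80% is then not the power of the design as described. The same paragraph is also the starting point for the planned check on baseline data. Whether one starts from 40 or from 45 patients per cluster changes the recruitment requirement by about 150 patients before any baseline ICC has been seen. The cluster counts add a second, smaller question, because the printed cluster size does not reproduce 38.

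**Working it through.** **Inputs** (all from the Sample size section): difference/SD = 0.1/0.3 = 0.5/1.5 = 1/3; power 80%; two-sided 5%; ICC 0.1; cluster size m = 40; dropout 5%.

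**1. Individually randomized size.** The normal approximation, 2 × (1.960 + 0.842)² × 3², gives 141.3 per group. The t-test version gives 142.2, rounded up to 143. The plan's 143 is reproduced.

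**2. The plan's totals from its own factor.** 2 × 143 × 5.4 = 1,544.4, so 1,545. Then 1,544.4 / 0.95 = 1,625.7, so 1,626. Both totals are reproduced, so the break lies at the factor itself.

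**3. The factor.** Design effect = 1 + (m − 1) × ICC = 1 + 39 × 0.1 = 4.9. To obtain 5.4 one needs one of the following:

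- m = 1 + 4.4/0.1 = 45 with ICC 0.1;
- ICC = 4.4/39 = 0.113 with m = 40;
- with unequal clusters, 1 + ((1 + CV²)m − 1) × ICC = 5.4, which gives CV² = 45/40 − 1 = 0.125 and CV about 0.35.

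**4. The same chain with 4.9.** 2 × 143 × 4.9 = 1,401.4, so 1,402 evaluable; 1,402 / 0.95 = 1,475.8, so 1,476 recruited. The printed totals are about 10% higher (1,545/1,402 = 1.10), a difference of 150 recruited patients.

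**5. Power of the printed size.** Effective n per group = N / (2 × design effect). Noncentrality = (1/3) × √(effective n / 2). The t reference uses clusters minus 2 degrees of freedom.

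| Design | Factor | Effective n per group | Power, normal | Power, t |
|---|---|---|---|---|
| 1,545 evaluable, m = 40, 38 clusters | 4.90 | 157.7 | 84.1% | 82.1% |
| 1,545 evaluable, 42 equal wards (36.8 each) | 4.58 | 168.7 | 86.5% | 84.8% |
| 1,402 evaluable, m = 40, 36 clusters | 4.90 | 143.1 | 80.5% | 78.2% |

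**6. Cluster counts.**

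- Evaluable: 1,545/40 = 38.6, so at least 39 clusters are needed. 38 × 40 = 1,520, which is 25 patients (1.6%) short.
- Recruited: 1,626/40 = 40.65, so 41 wards, or 42 if the number is made even for two arms. At 42 wards there are 1,626/42 = 38.7 recruited and 1,545/42 = 36.8 evaluable patients per ward.
- If 45 per cluster was meant: 1,545/45 = 34.3 and 1,626/45 = 36.1, so 35 and 37 clusters. These match neither printed count.

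**The case against.** The strongest reply is that nothing harmful follows. Under the stated ICC and cluster size the trial is larger than it needs to be, the 80% target is met, and the remark about a cautious choice of cluster size suggests a deliberate margin. The factor also carries a citation that is not available here and might use another formula. The first part stands: the error is conservative. The rest does not rescue the figure. The cautious choice concerns the number per cluster, and the number printed is 40. The text names only the ICC and the cluster size as inputs, so any further term would have to be stated.

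Four stronger readings are tempting, and the document does not support them.

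- *The trial is underpowered.* With a cluster-size CV of 0.35, power for 38 clusters would be about 78% (t). That CV is solved backwards from 5.4 and appears nowhere in the protocol.
- *The 42 wards are wrong, because 42 × 40 = 1,680.* A ward count and a patient total do not require exactly 40 patients in every ward, and 42 can be read as 40.65 rounded up to an even number.
- *The baseline check cannot be interpreted.* The difference, SD, ICC, cluster size, power and dropout are all stated, so it can be redone with observed values without the old factor.
- *Recruitment could be cut by 150.* By the t reference, 1,402 patients in 36 clusters have only about 78% power.

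**Conclusion.** The point holds as an arithmetic inconsistency in a figure that the plan relies on. Under the standard design effect, ICC 0.1 and 40 per cluster give 4.9, not 5.4, and the discrepancy raises both totals by about 10% over what the stated inputs require. It works in the trial's favour: power for 1,545 evaluable patients in 38 clusters is about 82% (t) to 84% (normal). This assumes equal, independently randomized clusters of 40 and the stated ICC. If about 45 per cluster was intended, 1,545 does give about 80% by the normal approximation (80.5%), and the printed cluster size and counts are then the wrong figures. The document does not show which was meant. The count of 38 is a minor rounding-down; 42 is not an error in itself.

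**What to change.** Keep 1,626 patients in 42 wards and reconcile the paragraph in one of two ways.

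- (a) State the cluster size, or the variation in cluster size, that produces 5.4, and give cluster counts that match it.
- (b) Use 1 + (m − 1) × ICC with the planned evaluable number per ward, about 37, so that the factor is about 4.6, and restate the power.

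Replacing 5.4 by 4.9 while leaving 1,545 and 1,626 in place is not enough, because the chain would still not add up.

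Calculate the restated power with a t reference on the number of independently randomized units minus 2, and allow for unequal cluster sizes. Because wards sharing a senior physician are randomized together, there may be fewer than 42 independent units. About 85% is therefore an upper figure, valid only for 42 equal, independent wards, and should not be printed as the power of the trial without that check. The cost is rewording one paragraph, with no extra patients.
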